### OAR doses

OAR doses are listed in the section “Figures, Tables and Additional Files”. OAR doses may not be exceeded except in the case of chest wall/rib(s) involvement. In cases where the PTV coverage cannot be achieved without exceeding OAR doses, the PTV coverage is to be compromised. All serial organized OARs within 5 cm of the PTV must be contoured (partial organ contours allowed); for parallel organized organs (liver, lung, etc.) within 5 cm of PTV, the whole organs need to be contoured. This should be tested for each PTV by creating a 5 cm expansion to examine which OARs lie within that expansion. This applies to volumetric modulated arc therapy deliveries only. For static, multi-beam field deliveries, care should be made to ensure all organs that intersect the beam meet dose constraints (i.e. no unanticipated hot areas along beam path, such as hot-spots in skin).

Organs that are under the influence of motion (i.e. respiratory) must be considered for the addition of a PRV, particularly for the motion encompassing (ITV) treatment delivery method. PRV size will be determined by radiation oncologist with input from physics. The approach to determining PRV margins must not differ between trial arms.

If OAR motions are affected by respiration (e.g. in treating thoracic or upper abdominal targets), the OARs should be contoured with the help of 4D-CT (and use of MIP for soft tissue OARs and MinIP for airways OARs).

Use of an OAR PRV (~2-3mm) should also be strongly considered if the risk of high grade toxicities is perceived to be high, for example when treating central lung lesions (esophagus, proximal trachea/proximal bronchial trees, pulmonary arteries), left lower lobe or left adrenal lesions (stomach if close to the target), or abdominal/pelvic lesions (GI tract OARs including esophagus, stomach, small/large bowels, central biliary tracts, etc).

For vertebral tumours, a spinal cord PRV is strongly recommended. For other sites, either a spinal cord PRV or a spinal canal contour are acceptable.

### Treatment planning

Treatment can be delivered using static beams (either 3D-conformal radiotherapy or intensity-modulated) or rotational therapy (volumetric modulated arc therapy, 3D conformal arcs or tomotherapy). Systematic differences in treatment techniques between trial arms for a particular treatment site are not permitted.

OAR dose constraints may not be exceeded (except chest wall/ribs). If a dose constraint cannot be achieved due to overlap of the target with an OAR, the fractionation (for patients in Arm 1) can be increased, or the target coverage compromised in order to meet the constraint. In cases where the target coverage or dose must be reduced, the priority for dose coverage is the GTV (e.g. attempt to cover as much of the GTV as possible with the prescription dose). All such cases of dose reduction or target coverage compromise must be approved by the local PI prior to treatment.

For patients treated with radiation previously using a different fractionation, similar biologically effective dose calculations should be used to equate previous doses to the tolerance doses listed in Appendix 1 and 2 (with the exception of mean lung dose tolerances, which may be excluded in the context of prior conventionally fractionated radiation doses summed with SABR treatment doses). Equivalent Dose in 2 fractions (EQD2) is the standard radiobiology conversion for overlapping treatment plans contributing to an accumulated dose (sum). An α/β = 2 for cord/brainstem/nerve structures and α/β =3 for all other normal tissues is the current standard.

“Hot Spot” is defined as the dose to 0.035cc volume.

For all targets, doses should be prescribed to either using: 1) the prescription isodose method or 2) the dose-volume method. For prescription isodose method, dose is prescribed to the 60–90% isodose line surrounding the PTV, and all hotspots should fall within the GTV or ITV. For the dose-volume method, ≥ 95% of the PTV should be covered by 100% of the prescription dose, and at least 99% of the PTV should be covered by 90% of the prescription dose. The hot spot should be less than or equal to 150% of the prescription dose (at treating physician’s discretion, up to 167% is acceptable) and should fall within the GTV or ITV.

For spine metastases, it is recommended to keep the hotspots of CTV not including “GTV + 2 mm” to < 110%, to reduce the risk of vertebral compression fracture (VCF).

It is recommended to use the PRV and strict Image-guided radiation therapy (IGRT) credentialing to have strong confidence with small uncertainty that the maximum doses are not much higher than the prescribed volume.

Dose calculation algorithms should be “Type B” (convolution/superposition) or “Type C” (radiation transport equations or Monte Carlo). Doses must be corrected for inhomogeneous tissues (i.e. lung, bone). Dose grid resolution should be ≤ 2.5 mm. For spine and brain a dose grid of ≤ 1.25 mm is recommended. Dose calculation algorithms may differ between treatment sites (for example Type C may be used in lung but not in the pelvis) but are not permitted to differ between trial arms for the same site.

The number of isocentres is at the discretion of the treating physician, physicists, and dosimetrists. Generally, metastases are treated with separate isocentres if they are well-separated. Single isocentre, multiple PTV plans are allowed if approved by physics.

Image guidance is required for SABR delivery. Cone Beam CT (CBCT) volumetric imaging is recommended, but orthogonal KV imaging is allowed per discretion of medical physicist, physician and treating radiation therapists.

Image guidance (kV vs. CBCT) must not systematically differ between trial arms. However, for SF SABR (Arm 2), if intrafraction motion assessment and management (e.g., surface-guided RT, tumour tracking, etc.) is not available, the addition of repeat image guidance and re-positioning at mid-treatment is strongly recommended to correct for the increased risk of intrafraction motion.

The scheduling and sequence of treating each metastasis is at the discretion of individual physicians, but in general should begin with the brain, due to risks associated with progression. Radiation schedule will depend on sites of tumour being treated, but generally daily or every other day for 1-3 weeks.

### Quality Assurance (QA) (arms 1 & 2)

In order to ensure patient safety and effective treatment delivery, a robust quality assurance protocol is incorporated. The following requirements must be completed for each patient:Prior to treatment, each patient must be discussed at QA rounds or be peer reviewed by a radiation oncologist with SABR expertise.All RT plans must meet target dose levels for OARs (except chestwall/ribs) (section “Figures, Tables, and Additional Files”). Prior to plan approval, the dose to each OAR must be reviewed by the physicist or treating physician.All treatment plans must undergo physics QA review per institutional practice. The QA review must include the treatment beam monitor unit verification.All SABR treatments must be delivered on a RT linac commissioned for SABR use and complies with a QA schedule as recommended by current international published guidelines [22].

### Systemic therapy

Patients treated with prior systemic therapy are eligible for this study, however, no chemotherapy agents (cytotoxic, or molecularly targeted agents) are allowed within the period of time commencing one week prior to radiation lasting until one week after the last fraction. Hormonal therapy is allowed. Use of chemotherapy schemes containing potent enhancers of radiation damage (e.g. gemcitabine, adriamycin/doxorubicin, bevacizumab) should not be used within one week prior to SABR and are discouraged within the first four weeks after radiation (i.e. omit one cycle).

### Further RT for progressive disease at new metastatic sites

Patients in Arm 1 who develop new, untreated metastatic deposits should be considered for MF SABR at those sites, if such deposits can be treated safely with MF SABR, and if the treating institution offers MF SABR for that body site. If MF SABR is not possible, then SF SABR or palliative RT can be delivered as clinically appropriate.

Patients in Arm 2 who develop new, untreated metastatic deposits should be considered for SF SABR at those sites, if such deposits can be treated safely with SF SABR, and if the treating institution offers SF SABR for that body site. If SF SABR is not possible, then MF SABR or palliative RT can be delivered as clinically appropriate.

### QA for institutions joining study

Prior to opening the study, each participating research institution will be required to send to the Sponsor Investigator a mock treatment plan for the anatomic sites that will be treated (e.g. lung, brain, liver, adrenal), to ensure that the treatment plans are designed in compliance with the protocol. The local PIs will provide pertinent CT datasets. Each participating research institution can choose which tumour sites will be treated at their individual institution (i.e. some institutions may only choose to treat a subset of the eligible metastatic sites). Sites that have prior accreditation for SABR through a clinical trial (e.g. SABR-COMET, or organ-specific SABR trials) are exempt from this requirement for the organ sites that have been accredited in those trials.

### QA for 2^nd^ randomization

Clinical trial staff will provide a 5-20 minute training session to participants randomized to Arm B on how to use a patient outcomes management tool for self-reporting of symptoms at time of enrollment. Electronic entry platform will be configured to send an email alert to a HCP when a patient-reported symptom meets notification criteria.

## Patient discontinuation / withdrawal

Patients may discontinue participation in the study at any time. The clinical and laboratory evaluations that would have been performed at the end of the study should be obtained. If a subject is removed because of an adverse event, they should remain under medical observation as long as deemed appropriate by the treating physician. Patients withdrawn or discontinued can be replaced at the discretion of the Study Principal Investigator [14].

## Follow-up evaluation and assessment of efficacy

There is no planned follow-up at the end of the study. Additional care that will be provided to subjects, after they complete or discontinue the study, will involve the standard of care treatment for what is normally expected for their condition.

## Statistical considerations

### Randomization

#### 1^st^ randomization

The study will employ a 1:1 randomization between Arm 1 and Arm 2, with further stratification between 1) systemic therapy within last two weeks (yes vs. no), 2) number of sites to be treated with SABR (one vs. multiple) and 3) SABR to abdominal sites (yes vs. no).

Permuted block randomization will be used to reduce selection bias, promote allocation concealment, and improve balance across groups over the trial period. Patients will be randomized based on a permuted block design using a block size based on a multiple of 3 (with block size known only to statistician until analysis is completed [23]. The Coordinating Centre and trial statistician will be responsible for configuring the module within REDCap, the electronic data capture (EDC) system that will be used to randomize participants.

#### 2^nd^ randomization

The 2^nd^ randomization of the study will also employ a 1:1 randomization between Arm A and Arm B, with stratification by sex (female vs. male vs. other).

### Sample size calculation

#### 1^st^ randomization

The sample size is based on toxicity of SABR (grade 3-5 AEs possibly, probably, or definitely related to SABR collected by HCP). The previously published SABR-5 protocol pre-defined a 10% rate of grade ≥ 4 AEs as acceptable, and we will conservatively set a 10% grade ≥ 3 AE rate as acceptable for this study [8]. The standard and intervention arms will be accrued 1:1. Sample sizes of 299 in Arm 1 and 299 in Arm 2 are required to achieve 80% power to detect a non-inferiority margin difference of 5%, with the reference group grade ≥ 3 AEs set at 5% based on the results of SABR-5. Based on our clinical judgement, the treatment group is assumed to be 10% under the null hypothesis of inferiority and coincides with our pre-defined < 10% grade ≥ 3 AE rate. The power was computed for the case when the actual treatment group proportion is 5%. This was based on a one-sided z test (unpooled) and alpha of 0.025.

In addition, given the importance of efficacy as a secondary outcome, we wanted to ensure that this sample size would have sufficient power to rule out large effect size differences in LCR. Based on our SABR-5 trial data, the estimated LCR at 1 year is 90%. With 584 patients, assumed to be accrued over five years with an additional five years of follow-up, then we would achieve > 80% difference to rule out a non-inferiority hazard ratio margin of 1.32 (which is equivalent to SF arm having a 1-year LCR of 87%). Hence, this sample size is sufficient to provide evidence of non-inferiority for efficacy.

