### Primary endpoints

The primary outcome for the first randomization is HCP-reported toxicity including grade 3-5 adverse events that are possibly, probably, or definitely related to SABR using CTCAE version 5.0. HCP-reported toxicity will be collected at study visits using the AE form. AEs will be compared at the per patient level at any time point post-treatment. Overall rate of AEs is calculated based on the greatest reported severity of SABR-related AEs over the course of the study for each patient. Differences in rates of grade 3 or higher toxicity between groups will be tested using the chi-square test or Fisher’s exact test, as appropriate. Non-inferiority will be assessed using the Farrington-Manning test.

Primary outcome for the 2^nd^ randomization is participant-reported QoL as measured by the EQ-5D-5L. Differences in participant-reported QoL between groups will also be tested using the chi-square test or Fisher’s exact test, as appropriate with non-inferiority assessed using the Farrington-Manning test.

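### The stated 80% power for the primary toxicity endpoint belongs to an unpooled z test; the planned Farrington-Manning test has about 77% with 299 evaluable patients per arm

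*Protocol article*

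**What the plan says.** In the Protocol article, under Sample size calculation (1st randomization), the size and power are given together: "Sample sizes of 299 in Arm 1 and 299 in Arm 2 are required to achieve 80% power". The margin is an absolute difference of 5 percentage points ("to detect a non-inferiority margin difference of 5" percent). The multi-fraction rate is fixed at 5% ("with the reference group grade ≥ 3 AEs set at 5% based on the results of SABR-5"). At the null boundary, "the treatment group is assumed to be 10% under the null hypothesis of inferiority". The alternative is no difference: "The power was computed for the case when the actual treatment group proportion is 5" percent. The test is then named: "This was based on a one-sided z test (unpooled) and alpha of 0.025".

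Under Primary endpoints, the article compares the rates of grade 3 or higher toxicity with a chi-square or Fisher test, and adds for the non-inferiority question: "Non-inferiority will be assessed using the Farrington-Manning test".

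The section on the 2nd randomization gives the trial total as 598, which is 2 × 299.

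**The concern.** The article fixes two different tests for one hypothesis: one to size the trial and one to decide it. The chi-square or Fisher test does not bridge them, since it addresses a difference in rates and not the margin. Farrington-Manning is therefore the deciding test, and the power that matters is its power.

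The two tests use different standard errors. The unpooled z test takes the variance at the observed rates. Farrington-Manning takes it at the rates that fit best when the two arms are forced to differ by the margin. At low event rates with a margin as large as the reference rate, the second variance is clearly larger, so the same data give a smaller test statistic and less power.

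At stake is an accurate statement of the risk of missing true non-inferiority on the endpoint that sets the size of the whole trial.

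**Working it through.** **Inputs** (all from Sample size calculation, 1st randomization): n = 299 per arm, 1:1; rate 5% in each arm under the alternative; 10% versus 5% at the null boundary; margin d = 0.05; one-sided alpha 0.025, so z = 1.96; power 80%, so z = 0.8416.

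**1. Reproduce the stated figure with the unpooled z test.**

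n = (1.96 + 0.8416)² × 2 × 0.05 × 0.95 / 0.05² = 298.3, rounded up to 299.

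Power at 299: the standard error is √(0.095/299) = 0.01783, and Φ(0.05/0.01783 − 1.96) = 80.1%. Full enumeration of the two binomial distributions gives 80.5%. The stated figure is right for the test it names.

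**2. Farrington-Manning variance.**

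With 5% observed in both arms, the maximum-likelihood rates constrained to differ by 0.05 are 8.49% (single fraction) and 3.49% (multi-fraction). The closed form and numerical maximisation agree.

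- Variance sum under the restriction: 0.0849 × 0.9151 + 0.0349 × 0.9651 = 0.1113
- Variance sum at 5% and 5%: 0.0950
- Standard errors at 299 per arm: √(0.1113/299) = 0.01930 against 0.01783

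**3. Farrington-Manning power at 299 per arm.**

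- Asymptotic formula: Φ[(0.05 − 1.96 × 0.01930)/0.01783] = Φ(0.683) = 75.3%
- Full enumeration of two Binomial(299, 0.05) counts, claiming non-inferiority when Z ≤ −1.96: 76.7%
- Simulation of 400,000 trials: 76.7%

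**4. Size needed for 80% with Farrington-Manning.**

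- Asymptotic formula: (1.96 × √0.1113 + 0.8416 × √0.0950)² / 0.05² = 333.7, so 334 per arm
- Enumeration: 79.8% at 325, 80.2% at 327, 80.6% at 330. Exact power moves in small steps with n, so about 327 per arm is the fair reading.

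This is 28 to 35 more per arm, or 654 to 668 in total against 598.

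**5. Exact type I error at 10% versus 5%, 299 per arm.**

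| Test | Power at 5%/5% | Type I error (nominal 2.5%) |
|---|---|---|
| Unpooled z | 80.5% | 2.84% |
| Farrington-Manning | 76.7% | 2.42% |

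The unpooled test reaches its 80% while exceeding its nominal error rate.

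**The case against.** The strongest reply is that the effect is small and the document is open about its method. It names the test behind the 80%, and the arithmetic for that test is correct. The shortfall is 3.3 points by enumeration, less than the change produced by modest uncertainty in the planning rate: with 299 per arm, Farrington-Manning power is 83.8% if the true rate in both arms is 4%, 80.1% at 4.5% and 70.3% at 6%. The planned test also controls its type I error. All of this stands, and it limits the point to a correction of a stated property. It does not remove the mismatch, because the article assumes 5%, and at 5% its own deciding test does not have 80% power.

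Three stronger readings are tempting, and the document does not support them.

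- **That the sample size is miscalculated.** It is not; 299 reproduces exactly. The sizing test differs from the analysis test.
- **That the plan makes no provision for patients who cannot be evaluated.** The total has no built-in allowance, but the section on patient discontinuation and withdrawal lets the study's principal investigator replace such patients at discretion. The endpoint is the worst grade at any time after treatment, so a treated patient with partial follow-up can still contribute. Any loss rate would be an assumption. With 5% lost and not replaced (284 per arm), power would be 74.3%, but the article gives no basis for that 5%.
- **That the primary test wrongly ignores the stratification.** Randomization is stratified ("with further stratification between 1) systemic therapy within last two weeks (yes vs. no", plus number of sites and abdominal SABR), and the log-rank test for PFS and OS is stratified. On the toxicity test the article is silent about strata. Silence does not make the test unstratified, and this is a detail that the full protocol or SAP may settle.

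**Conclusion.** The point holds. At the article's own assumptions, the 80% applies to the unpooled z test only. The Farrington-Manning test has about 77% power with 299 evaluable patients per arm (76.7% by enumeration, 75.3% asymptotically). The chance of missing true non-inferiority is therefore about 23%, where 20% is implied.

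This rests on a true rate of 5% in both arms and on every patient being evaluable. Since 598 is exactly 2 × 299, any patient who is not evaluable and not replaced lowers power further, by an amount the document does not let us fix.

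The planned analysis remains valid and no bias follows. The error is in the stated power, and it is worth correcting because it concerns the primary hypothesis and the basis of the trial's size.

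**What to change.** Keep Farrington-Manning as the primary non-inferiority test. In Sample size calculation (1st randomization), replace the unpooled z test as the basis of the power statement. State that 299 evaluable patients per arm give about 77% power with Farrington-Manning at 5% in both arms, a 5-point margin and one-sided alpha 0.025. Do not resolve the mismatch by moving the analysis to the unpooled z test, since its exact type I error is above the nominal level in a comparison about safety.

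This is a text change with no effect on conduct; its cost is a stated power about 3 points lower. If the sponsor wants to hold 80%, about 327 to 334 evaluable patients per arm would be needed.

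As an optional refinement, separate from the error, the sponsor could use a score test stratified on the randomization factors. The gain is likely to be small and cannot be quantified from the document, which gives no rates by stratum. About 30 events are expected (598 × 0.05) over eight strata (2 × 2 × 2), fewer than four per stratum on average, so a rule for collapsing sparse strata would have to be set in advance.

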#### 2^nd^ randomization

The sample size is based on hypothesized QoL differences (mean difference of 5.7) between the intervention arms based on the landmark Basch et al. study, as well as the unpublished standard deviation of 15.6 for EQ-5D-5L scores from our ongoing SABR-COMET-3 study to capture expected standard deviation for our patient population [13, 14]. Group sample sizes of 125 and 125 will provide 80% power to detect a significant difference based on an alpha of 0.05. We will plan an analysis of Arm A and B after 250 patients.

The total sample size for this trial is 598 based on the primary objective of the first randomization.

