### Survival and secondary endpoints

PFS and OS will be calculated using the Kaplan-Meier method with differences compared using the stratified log-rank test. Pre-planned subgroup analysis will occur based on the stratification factors, and also based on the use of immunotherapy vs. non-immunotherapy systemic agents. A multivariable Cox proportional hazards regression analysis will be used to determine baseline factors predictive of survival endpoints. For the endpoint of time to new metastases, a Fine and Gray competing risk analysis will be used to account for competing risk of death from any cause.

LCR will be calculated using the cumulative incidence function including mortality as competing risk.

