### Data Safety Monitoring Committee (DSMC) and interim analyses

There will be four interim analyses. The DSMC will conduct the first interim analysis once 50 patients are accrued. For this analysis, the DSMC will be blinded to the identity of each treatment arm, but OS and toxicity data will be presented for each arm (Arm 1 and 2), and treatment doses and volumes will be presented for SAEs reviewed. There are three planned interim analyses for efficacy in addition to the final analysis. The first two interim analyses are expected to be carried out when the total number of observed study deaths reaches 50 and 100, thus treatment details will be reviewed to determine plausible causation of toxicities. As such, interim efficacy analyses will not be blinded. The DSMC will recommend stopping the trial if there is an OS difference that is statistically significant with a threshold of p < 0.001 using the stratified log-rank test. The third interim analysis will be carried out after 50% accrual, or 250 patients to review QoL for Arm A and B. If the analysis yields significant results, we will select the superior arm and assign all patients moving forward to that group for the remainder of the trial duration. However, if results are not significant, we will continue to randomize patients to either Arm A or B until study completion. This will not affect the 1st randomization between Arms 1 and 2.The final analysis is expected to be carried out 3 years after the enrollment of the last subject.

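### The greater than 80% power claimed for lesional control needs an unstated one-sided 0.05, five years of further follow-up and no deaths; at the stated 3-year final analysis it is about 61% to 72% before deaths

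*Protocol article*

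**What the plan says.** In the Protocol article, Sample size calculation, 1st randomization, the second paragraph takes a 1-year LCR of 90% from SABR-5 and sets out its design assumptions as "With 584 patients, assumed to be accrued over five years with an additional five years of follow-up". The power claim drawn from these assumptions is that "we would achieve > 80% difference to rule out a non-inferiority hazard ratio margin of 1.32". The word printed as difference evidently means power. The margin is said to correspond to a 1-year LCR of 87% in the single-fraction arm. The paragraph ends that "this sample size is sufficient to provide evidence of non-inferiority for efficacy". It gives no alpha and no allowance for death or dropout.

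Three other places bear on this:

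- The preceding paragraph, on toxicity, uses a one-sided test at alpha 0.025. This is the only non-inferiority alpha in the article.
- Sample size calculation, 2nd randomization: "The total sample size for this trial is 598 based on the primary objective of the first randomization".
- Data Safety Monitoring Committee (DSMC) and interim analyses: "The final analysis is expected to be carried out 3 years after the enrollment of the last subject".

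Survival and secondary endpoints adds that "LCR will be calculated using the cumulative incidence function including mortality as competing risk".

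**The concern.** The power statement assumes five years of follow-up after accrual closes, but the final analysis is set at three. For an endpoint with roughly a 10% failure rate per year, those two years carry a sizeable share of the events. The calculation also appears to have no deaths in it, although the analysis section treats death as a competing risk and the DSMC section schedules looks at 50 and 100 deaths.

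The article calls efficacy an important secondary outcome, lists LCR among its non-inferiority objectives in Methods, and in the Discussion foresees a recommendation if the single-fraction regimen is not inferior. A reader told that the trial is large enough to show non-inferior efficacy would misread an inconclusive LCR result, which could easily arise even if the arms were truly equal.

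**Working it through.** **Inputs.** From the article: 1-year LCR 90%; margin HR 1.32; 1:1 allocation; accrual A = 5 years; follow-up after accrual F = 5 years (sample size section) or 3 years (DSMC section); N = 584 or 598. My assumptions: exponential local failure, uniform accrual, no dropout, true HR of 1.

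**Margin.** λ = −ln 0.90 = 0.1054 per year. ln 0.87 / ln 0.90 = 1.322, and 0.90^1.32 = 0.870. The two forms of the margin agree.

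**Formulas.** With death hazard μ and L = λ + μ:

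- P(event) = (λ/L) × [1 − (e^(−LF) − e^(−L(F+A))) / (A·L)]
- D = N × P(event)
- Power = Φ(ln 1.32 × √D / 2 − z), with ln 1.32 = 0.2776 and z = 1.960 (one-sided 0.025) or 1.645 (one-sided 0.05)
- Events for 80% power = 4 × [(z + 0.842)/0.2776]², which is 408 at 0.025 and 321 at 0.05

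**1. The plan's own figure (584, F = 5, μ = 0).** P = 1 − (0.5905 − 0.3487)/0.5268 = 0.541, so D = 316. Power is Φ(2.467 − 1.645) = 79.5% at 0.05 and Φ(2.467 − 1.960) = 69.4% at 0.025. Variants:

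| Variant, F = 5, no deaths | 0.025 | 0.05 |
|---|---|---|
| N = 584, true HR 1 | 69.4% | 79.5% |
| N = 598, true HR 1 | 70.4% | 80.3% |
| N = 584, events counted with one arm at HR 1.32 | 73.2% | 82.5% |
| N = 598, events counted with one arm at HR 1.32 | 74.2% | 83.3% |

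The stated figure is therefore recovered at one-sided 0.05 and in none of these variants at 0.025.

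**2. The stated final analysis (598, F = 3, μ = 0).** P = 1 − (0.7290 − 0.4305)/0.5268 = 0.433, so D = 259. Power is 60.8% at 0.025 and 72.2% at 0.05. With 584 patients it is 59.8% and 71.3%. Counting events with one arm at HR 1.32 (598 patients, 287 events) gives 65.2% and 76.0%. All are below 80%.

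**3. Adding deaths (598, F = 3).** The article gives no mortality rate, so the median overall survival (OS) is assumed, with μ = ln 2 / median.

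| Assumed median OS | Events | 0.025 | 0.05 |
|---|---|---|---|
| No deaths | 259 | 61% | 72% |
| 13.5 years | 228 | 55% | 67% |
| 6 years | 196 | 49% | 62% |
| 4 years | 173 | 45% | 57% |
| 3 years | 154 | 41% | 53% |

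Keeping F = 5 with 598 patients does not restore the claim once deaths enter: a median OS of 13.5 years gives 275 events, and 63% or 74%.

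**4. What can be excluded with 80% power (598, F = 3, no deaths).** HR = exp[2(z + 0.842)/√259] = 1.42 at 0.025 and 1.36 at 0.05. The corresponding 1-year LCRs in the single-fraction arm are about 86.1% and 86.6%, against the 87% quoted.

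**The case against.** The strongest reply is that the stated figure reproduces. The alpha of 0.025 closes the toxicity paragraph and describes a test of two proportions; nothing extends it to LCR. At one-sided 0.05 the article's inputs give 79.5%, or 80.3% with the actual 598. This stands. A reader might infer that the greater than 80% is an arithmetical error, and the article does not support that. What can be said of the calculation as stated is that its alpha is missing and, if it was 0.05, looser than that of the primary test.

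Three further points also stand:

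- Using 584 instead of 598 is conservative. It is an editorial inconsistency and contributes nothing to the shortfall.
- Mortality is assumed. A reader might take the lower power figures, or a statement that LCR would be inconclusive about half the time, as a fact about this trial. They are conditional on the survival chosen. Without deaths, the chance of missing non-inferiority with equal arms at 3 years is about 39% (0.025) or 28% (0.05). The 61% is likewise a figure before deaths, not after them.
- If the 90% is already a cumulative incidence with death competing, my model slightly understates events. Recalibrating to a 10% one-year incidence gives 205 to 169 events for median OS of 6 to 3 years, and 51% to 44% power at 0.025, instead of 49% to 41%. The shift is small.

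None of this answers the conflict over follow-up. At 3 years power is below 80% at both alphas before a single death is counted.

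**Conclusion.** The point holds in this form. The greater than 80% power requires an unstated one-sided 0.05, a follow-up that contradicts the DSMC section, and no deaths, all together. At the stated final analysis, with 598 patients and no deaths, power at HR 1.32 is about 61% (0.025) or 72% (0.05). With an assumed median OS from 13.5 down to 3 years, it is about 55% to 41%, or 67% to 53%. The no-death figures rest on exponential failure, uniform accrual and truly equal arms; the with-death figures rest also on mortality that the article does not supply. The conclusion that the sample size suffices for efficacy non-inferiority is not supported at the planned analysis.

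A reader might go further and conclude that the trial is underpowered overall or needs more patients. The article does not support that: the sample size is set by toxicity, and LCR is a secondary endpoint. This is a correction to a stated figure and leaves the primary test untouched.

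**What to change.** In the LCR paragraph of the sample size section:

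1. Reconcile the five-year follow-up with the 3-year final analysis. Either recompute at 3 years, or state in both sections that LCR is analysed at 5 years.
2. State the one-sided alpha for the LCR comparison.
3. Use 598 patients.
4. Give an explicit death assumption with its source, and say whether the 90% is net of competing deaths.
5. Restate either the power at HR 1.32 or the hazard ratio that can be excluded with 80% power. At 3 years before deaths the latter is about 1.42 (0.025) or 1.36 (0.05), and it is larger once deaths are included.
6. Correct the word difference to power, and withdraw or qualify the sufficiency sentence. Moving LCR to 5 years does not remove the need for this, because any realistic mortality still has to be entered.

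The cost is a text amendment and a less favourable published figure. Enrolment and the primary toxicity analysis do not change. Moving the LCR analysis to 5 years would add two years of follow-up for that endpoint.
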